**Method/design:**

The study is designed as a dual center, two-armed, observer-blinded, randomized controlled trial. Relatives are randomized to participate in one of two conditions: either four sessions of manualized family psychoeducation or four sessions in a social support group led by a health care professional. Patients will not participate in the groups and will continue their treatment as usual. A total of 100 patients, each accompanied by one relative, will be recruited primarily from two outpatient clinics in the Capital Region of Denmark.

The primary outcome is the occurrence of depressive relapse at 9-month follow-up defined as a score ≥7 on the Hamilton six-item subscale. Secondary outcomes will include time to relapse.

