### Aim

The aim of the present study is to compare an intervention consisting of FPE to an active control intervention of social support for relatives of patients with a diagnosis of major depression.

The following hypotheses are proposed:Psychoeducational intervention for relatives will reduce the risk of depressive relapse (defined as a score on The Hamilton six-item subscale, HAM-D_6_ ≥ 7), among remitted depressed patients (HAM-D_6_ < 7) compared to the active control conditionPsychoeducational intervention for relatives will reduce the time to achieve full symptomatic remission (defined as HAM-D_6_ < 5) among partially remitted depressed patients (HAM-D_6_ = 8–12) compared to the active control conditionPsychoeducational intervention for relatives will reduce depressive symptoms (measured on the HAM-D_6_) among currently depressed patients (HAM-D_6_ ≥ 13), compared to the active control condition

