### Outcomes

#### Primary outcome

The primary outcome is occurrence of depressive relapse defined as a score ≥7 on the HAM-D_6_ [54] in the 9-month follow-up period (hypothesis 1) among remitted patients.

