### Statistics

#### Sample size calculation

Regarding the testing of hypothesis 1, only one similar study in the literature exists that tests an invention similar to the one applied in our study. Shimazu et al. [19] here found a relapse rate in the 9-month follow-up period of 8 % in the intervention group and 50 % in the control group. Based on these findings, 21 patients should be included in each group when using a power of 80 % and type-I error probability associated with the test of the null hypothesis of 5 %. However, we wish to make a more conservative estimate since we acknowledge that our active social support group may also have a positive impact on the outcome results. We therefore plan to include 30 patients in each group to the test hypothesis 1.

Regarding the testing of hypotheses 2 and 3, there are to the best of our knowledge no studies describing this type of intervention to this specific patient group. Therefore, a sample size calculation cannot be performed. Consequently the testing of hypotheses 2 and 3 is more exploratory and we plan to include 15–20 patients in each group to examine both these hypotheses.

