#### Statistical analyses

For the statistical analysis SAS software ® will be used.

Baseline characteristics of the invention group and the control group, respectively, will be compared using a *χ*^2^-test regarding categorical variables and an independent samples *t* test regarding numerical variables. The comparison of baseline characteristics will be performed for the whole group of patients independent of subgroup affiliation based on depression levels at baseline.

The number of recurrences in the two groups will be compared using the Mann-Whitney *U* test.

Time to relapse as well as time to full remission (for patients only partially remitted at baseline) will be analyzed using the Kaplan-Meier survival analysis.

To analyze whether the degree of EE in relatives at baseline will be associated with poorer outcome, Cox proportional hazard regression analysis will be applied.

Intention-to-treat analyses will be carried out, meaning that analyses will include all subjects who are randomized.

Regarding missing data the method of Last Observation Carried Forward (LOCF) will be applied.

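### The primary outcome is yes/no relapse, but the only between-arm test given for relapse frequency is a Mann-Whitney U test on an undefined number of recurrences

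*Protocol article*

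**What the plan says.** The protocol article defines the primary question in four places, each time as one yes/no result per patient:

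- Aim, hypothesis 1: "Psychoeducational intervention for relatives will reduce the risk of depressive relapse" among remitted patients.
- Primary outcome: "The primary outcome is occurrence of depressive relapse defined as a score" of 7 or more on the HAM-D6 during the 9-month follow-up, among remitted patients.
- Abstract, Method/design: "The primary outcome is the occurrence of depressive relapse at 9-month follow-up". The timing is worded slightly differently, but the outcome is still yes/no.
- Sample size calculation: relapse rates of "8 % in the intervention group and 50 % in the control group", from which "21 patients should be included in each group when using a power of 80" % and a 5% type-I error; this is raised to 30 per group.

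The section Statistical analyses assigns its methods as follows:

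- Relapse frequency, by a rank test: "The number of recurrences in the two groups will be compared using the Mann-Whitney".
- Chi-square and t tests: baseline characteristics only.
- Kaplan-Meier, for two secondary outcomes: "Time to relapse as well as time to full remission".
- Cox regression: whether expressed emotion at baseline is associated with poorer outcome.

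The number of recurrences does not appear under Primary outcome or Secondary outcomes and is not defined elsewhere.

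**The concern.** The endpoint and the test do not name the same quantity. A rank test on a count asks whether patients in one arm tend to have more recurrences than patients in the other. Hypothesis 1 asks whether fewer patients relapse. The two agree only if no patient can count more than once, and the article does not say so.

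The design leaves room for repeats. The HAM-D6 is taken by telephone every 6 weeks during follow-up, and relapse is also sought through patient contact and medical records. The text gives no rule for when one relapse ends and another begins. If repeats are counted, the comparison reflects both how many patients relapse and how often or how long they do so.

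This matters because hypothesis 1 is the only hypothesis with a sample-size calculation. Two analysts following the same sentence could run different primary tests and reach different conclusions.

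**Working it through.** **1. The plan's own sample size.** Inputs from Sample size calculation: p1 = 0.50, p2 = 0.08, power 80%, alpha 5% (two-sided assumed, since sidedness is not stated). The mean proportion is 0.29 and the difference d is 0.42.

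n = [1.96·√(2·0.29·0.71) + 0.8416·√(0.50·0.50 + 0.08·0.92)]² / 0.42² = 17.1, so 18 per group.

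With continuity correction: (17.1/4)·[1 + √(1 + 4/(17.1·0.42))]² = 21.6, so 22 per group.

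Exact power of the two-sided Fisher test is 0.81 at 20 per group and 0.83 at 21. The stated 21 is therefore consistent with a comparison of two proportions. At the planned 30 per group, exact power is 0.972 for uncorrected chi-square and 0.949 for Fisher.

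**2. If the count is 0/1.** With N patients in total, the Mann-Whitney statistic (tie-corrected, no continuity correction) equals chi-square × (N−1)/N. For 15/30 versus 3/30, chi-square = 11.43 (p = 0.00072), and 11.43 × 59/60 = 11.24 (p = 0.00080). Exact power at 30 per arm is 0.972 for both tests at 8% versus 50%, and 0.69 for both at 20% versus 50%. Nothing of practical size is lost.

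**3. If the count can exceed one: a fixed example.** In one arm, 15 of 30 patients have one recurrence each; in the other, 7 of 30 have three each.

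- Chi-square on any relapse: 60·(15·23 − 7·15)² / (30·30·22·38) = 4.59, p = 0.032. Fisher gives p = 0.060.
- Mann-Whitney on counts: U = 15·23 + ½·15·23 = 517.5, against 450 expected. The tie-corrected variance is (900/12)·[61 − (54,834 + 3,360 + 336)/(60·59)] = 3,335, so z = 67.5/57.7 = 1.17 and p = 0.24.

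The same data give different conclusions depending on how the sentence is read.

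**4. Range by simulation.** There are 30 per arm, two-sided 5%, and at least 4,000 trials per case. Assumption: each relapser has 1 + Binomial(6, (m−1)/6) positive ratings, with mean m and a maximum of 7. Chi-square is uncorrected. The chi-square and Fisher columns are exact values.

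| Relapse risk | Repeats among relapsers | Mann-Whitney on counts | Chi-square, any relapse | Fisher, any relapse |
|---|---|---|---|---|
| 50% / 50% | same (mean 2.5 in both) | about 5% | 5% | 3% |
| 50% / 50% | mean 1.5 vs 3.5 | about 33% | 5% | 3% |
| 20% FPE / 50% control | same (mean 2.5 in both) | about 69% | 69% | 60% |
| 20% FPE / 50% control | 3.5 FPE vs 1.5 control | about 41% (39% to 42% over repeated runs) | 69% | 60% |

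A second count model (1 + Binomial(3, m), where m is now a probability) shows the same pattern. At 50%/50% with m = 0.6 versus 0.05, rejection is 36% against 5% for chi-square. At 50% versus 25% with the same m = 0.2 in both arms, power is 50% against 52%.

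**The case against.** The strongest reply is that the article treats relapse as happening once per patient almost everywhere: occurrence in the outcome, a single time from baseline to relapse, and relapse rates in the sample size. On that reading the number of recurrences in each group means how many patients relapsed, and the Mann-Whitney test is chi-square under another name. This is a fair reading and may be what was meant, and it removes the numerical harm. It does not remove the mismatch. The sentence uses a different term from the outcome, sets no limit per patient, and picks a test that would be an unusual choice for a binary endpoint.

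The large figures also rest on assumptions. They need repeat ratings within an episode to count as separate recurrences, and mean counts that differ more than twofold between arms. No section supports either. With the same repeat pattern in both arms, the rank test keeps its 5% level and loses almost no power. Nor is the 33% a false-positive rate in the ordinary sense, because the simulated arms do differ in how much depression relapsers have. The right comparator for it is chi-square at about 5%, since Fisher is conservative at this size.

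Kaplan-Meier for time to relapse uses first relapses and is unaffected by repeats. It limits the harm but belongs to a secondary outcome, so it does not supply the missing primary comparison.

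The absence of a risk difference or interval is detail that an article may leave to the full plan, and is not part of this point.

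**Conclusion.** The mismatch stands. The article fixes a test for relapse frequency, and that test is not tied to its own primary outcome, hypothesis or sample size. This is a conflict in stated text rather than detail left to an analysis plan.

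Its size depends on what a recurrence is. It is close to nil if each patient counts at most once. It is small if repeats follow the same pattern in both arms. It is material only if repeats differ strongly between arms: up to about 33% rejection at equal relapse risk, or power down to about 41% at 20% versus 50%. These limits come from assumed count models, not from the documents.

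A reader might infer that the plan definitely ranks counts per patient, or that the powered comparison will not be the one made. The text does not establish either; it only fails to rule them out. The point is a correction that should be made, not a defect that invalidates the design. The sample-size figure itself is sound as a two-proportion calculation.

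**What to change.** In Statistical analyses, replace the sentence on recurrences with one that names the primary analysis: a comparison between arms of the proportion of remitted patients with at least one relapse (HAM-D6 of 7 or more) in the 9-month follow-up, by chi-square or Fisher's exact test, preferably reported with a risk difference and 95% confidence interval. State which of the two tests is used.

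Then either drop the number of recurrences, or define it (including when a new recurrence begins) and label it exploratory, where a Mann-Whitney test is acceptable. Use the term relapse throughout for the primary outcome.

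The cost is one or two sentences, settled before outcomes are analysed. No new data are needed. The planned 30 per group stands: at 8% versus 50% it gives exact power of 0.972 with chi-square and 0.949 with Fisher.

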**Table 1 Tab1:**
[figure not shown]
Flow diagram for enrollment, interventions and data collection at baseline and follow-up

*FAD* The Family Assessment Device (36-items), *FAS* The Family Attitude Scale, *FMSS* The Five Minute Speech Sample, *HAM-D*
_*6*_ Hamilton six-item subscale, *MINI* MINI International Neuropsychiatric Interview, *PC* Perceived Criticism Scale, *SAPAS* The Standardized Assessment of Personality-Abbreviated Scale, *SCL-90-R* The Symptom Checklist-90-Revised, *SDS* The Sheehan Disability Scale, *WHO-5* The World Health Organization Well Being Index

Furthermore, telephone calls will be made to patients every 6 weeks in the follow-up period in order to obtain information on the presence of depressive symptoms measured by the HAM-D_6_.

Patients will be told to contact the principal investigator when recognizing a worsening of depressive symptoms. Furthermore, the patients’ medical records will be screened in order to identify information on relapse. Both the relatives and private psychiatrists have the opportunity to contact the principal investigator if they suspect a depressive relapse.

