#### Secondary outcomes

Secondary outcomes are time to relapse, defined as the number of weeks from baseline to relapse; time to full remission defined as a HAM-D_6_ score <5 [54] among the partially remitted patients (hypothesis 2); and the reduction of depressive symptoms in the HAM-D_6_-score (hypothesis 3).

A number of exploratory questions will be examined in regard to the impact of the two interventions: for patients’ depressive symptoms (MDI), subjective wellbeing (WHO-5), disability (SDS), family functioning (FAD) and perceived criticism (PC), and for the relatives: subjective wellbeing (WHO-5), family functioning (FAD) and EE (FAS and FMSS).

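### Unrestricted LOCF codes patients lost without a recorded relapse as relapse-free to 9 months, which understates the primary relapse risk

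*Protocol article*

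**What the plan says.** Under Statistical analyses, the article states: "Regarding missing data the method of Last Observation Carried Forward (LOCF) will be applied". No other missing-data method is named, and the sentence is not confined to particular outcomes. The same section defines intention-to-treat as "meaning that analyses will include all subjects who are randomized", so patients who drop out stay in the denominator. Time to relapse and time to full remission "will be analyzed using the Kaplan-Meier survival analysis".

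The Primary outcome section reads: "The primary outcome is occurrence of depressive relapse defined as a score ≥7 on the HAM-D_6", counted over the 9-month follow-up period in remitted patients. The Aim section places hypothesis 1 "among remitted depressed patients (HAM-D_6_ < 7"), so these patients start below the relapse threshold.

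On ascertainment, the Assessments section plans a visit within 2 weeks of the last group session and a 9-month visit. It adds that "telephone calls will be made to patients every 6 weeks in the follow-up period", with HAM-D6 as the measure. Medical records are also screened for relapse. Patients are told to make contact if they worsen, and relatives and private psychiatrists may report a suspected relapse.

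**The concern.** LOCF is sometimes defended as neutral or cautious. For this endpoint it is neither. The outcome is the first crossing of a threshold by patients who all begin on the same side of it. Someone lost before a recorded relapse has a last score below 7, and carrying that score forward declares the rest of the 9 months relapse-free. The rule can turn an unseen relapse into a non-relapse, but not the reverse.

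Relapse risk is then too low in any arm with dropout, by an amount that depends on how many leave and how early. Equal dropout pulls the risk difference towards zero. Unequal dropout gives the arm with more losses an advantage that has nothing to do with treatment. With 30 patients per arm planned for hypothesis 1, a few such patients matter: 10 points is 3 patients.

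The same unrestricted sentence reaches the other hypotheses. Under hypothesis 2 it codes a patient lost before remission as not remitted. Under hypothesis 3 it freezes a symptom score that may still be changing.

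**Working it through.** **The plan's own figure.** The Sample size calculation section gives 21 per group for 8% versus 50%, 80% power and 5% type I error, raised to 30. The two-sided two-proportion formula gives 18 without and 22 with continuity correction. Fisher's exact test has 80.7% power at 20 per group and 82.5% at 21. The stated 21 is reproduced closely enough and is not in dispute.

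**Inputs.**
- From the article: relapse risks of 8% and 50%, 30 per arm, all randomized patients analysed.
- Assumed: dropout fraction *d* of 10% to 30% (the article gives none), constant relapse hazard, dropout independent of relapse, no relapse found after contact is lost, two-sided 5% test.

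**Formula.** Let *p* be the true 9-month risk and λ = −ln(1 − *p*). The risk seen under LOCF is

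(1 − *d*)·*p* + *d*·*q*,

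where *q* is the chance of relapse before dropout. For dropout uniform over follow-up, *q* = 1 − *p*/λ. If everyone leaves before any post-baseline rating, *q* = 0.

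- *p* = 0.50: λ = 0.6931, *q* = 1 − 0.50/0.6931 = 0.2787
- *p* = 0.08: λ = 0.0834, *q* = 1 − 0.08/0.0834 = 0.041

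**Balanced dropout, 20% in both arms, uniform.**
- Control: 0.8 × 0.50 + 0.2 × 0.2787 = 0.456
- FPE: 0.8 × 0.08 + 0.2 × 0.041 = 0.072

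**With the true effect at 8% versus 50%** (power by normal approximation for two proportions, 30 per arm):

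| Dropout FPE / control | Timing | FPE | Control | Difference (points) | Relative risk | Power |
|---|---|---|---|---|---|---|
| none | – | 8.0% | 50.0% | 42.0 | 0.160 | 96.7% |
| 20% / 20% | uniform | 7.2% | 45.6% | 38.4 | 0.158 | 94.1% |
| 20% / 20% | before any rating | 6.4% | 40.0% | 33.6 | 0.160 | 89.0% |
| 10% / 30% | uniform | 7.6% | 43.4% | 35.8 | 0.175 | 90.9% |
| 10% / 30% | before any rating | 7.2% | 35.0% | 27.8 | 0.206 | 76.5% |
| 30% / 10% | uniform | 6.8% | 47.8% | 41.0 | 0.143 | 96.4% |
| 30% / 10% | before any rating | 5.6% | 45.0% | 39.4 | 0.124 | 95.9% |

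Balanced dropout leaves the relative risk almost unchanged and shrinks the difference. Heavier loss in FPE exaggerates the benefit on the relative scale, although the difference still falls slightly below 42.0.

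**With no true effect and 10% versus 30% dropout**, the false difference is (0.30 − 0.10) × (*p* − *q*):
- Risk 50%, uniform: 0.2 × (0.50 − 0.2787) = 4.4 points
- Risk 50%, before any rating: 0.2 × 0.50 = 10 points
- Risk 8%, uniform: 0.2 × (0.08 − 0.041) = about 0.8 points
- Risk 8%, before any rating: 0.2 × 0.08 = 1.6 points

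The sign follows the arm with more dropout.

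**Check of the remedy.** In simulations of 400,000 patients per scenario with 20% uniform dropout, Kaplan-Meier with censoring at last contact gave 8.0% and 50.0%. Holding the same patients event-free to 9 months gave 7.2% and 45.6%.

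**The case against.** Four objections carry weight.

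**Other routes to a relapse.** A reader might infer that every patient who drops out is counted as relapse-free. The article does not support that. Record screening does not depend on the patient answering calls, and relatives and private psychiatrists can report. These routes reduce the bias. They do not remove it, because relapse is defined by a HAM-D6 score and the article does not say how information from records is converted to one.

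**Kaplan-Meier.** A reader might infer that the plan contradicts itself by combining LOCF with survival analysis. The article never says that LOCF is applied inside the Kaplan-Meier analyses, and censoring rules may properly sit in an analysis plan that is not shown. What stands is narrower: the LOCF sentence exempts nothing, so its scope should be stated.

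**Size.** The dropout rates are assumptions. The 10-point case needs every leaver to go before any post-baseline rating and the baseline score to be carried forward, which the article does not state. It also belongs to a 50% risk in both arms and should not be set against the 8% rate. A reader might infer a false benefit for FPE, but that needs heavier loss in the FPE arm. The design gives no particular reason to expect it: patients attend no groups, and the control arm has the same number and length of sessions.

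**The remedy.** If patients who leave relapse more often, censoring also understates the risk. This is correct, and it is why a sensitivity analysis belongs with the change.

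The effects on hypotheses 2 and 3 are secondary, since the article calls those tests more exploratory. Coding lost patients as not remitted is conservative within an arm.

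**Conclusion.** The point stands for the primary relapse proportion and for the unrestricted scope of LOCF. For patients who start below the threshold and are judged on any crossing in 9 months, the stated rule biases relapse risk in one direction, downwards.

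The size is unknown because no dropout rate is given. Under the assumptions above, moderate balanced dropout mainly attenuates: the difference falls from 42.0 to 38.4 points and power stays at 94.1%. Unbalanced dropout can mislead in either direction. If there is no true effect, it creates a difference of 4.4 to 10 points at 50% risk and about 0.8 to 1.6 points at 8% risk. These figures ignore relapses found through records or reports, which would make the bias smaller, and assume dropout independent of relapse.

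This should be fixed, but it does not by itself invalidate the trial.

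**What to change.** - Remove LOCF for the relapse and remission outcomes.
- State that time to relapse and time to full remission are censored at the last HAM-D6 contact.
- Estimate the primary 9-month relapse risk in each arm by Kaplan-Meier, or by multiple imputation from the 6-weekly HAM-D6 scores already planned.
- Add a sensitivity analysis such as missing = relapse, because censoring is unbiased only if dropout is independent of relapse.
- For the HAM-D6 score in hypothesis 3, use a mixed model for repeated measures with baseline as a covariate.

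The cost is revised wording, a little more programming and slightly wider intervals. No extra data collection is needed.

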## Discussion

To our knowledge this is the first randomized controlled trial comparing Family Psychoeducation (FPE) with an active control group in order to clarify the mechanism behind any observed change due to FPE as well as examining the long-term effect of this intervention for patients and relatives.

It is hoped that the intervention will impact positively on both patients and relatives by improving family functioning. Specifically, family psychoeducation is designed to provide the relatives with better strategies in order to cope and support depressed family members, thereby facilitating a quicker response to treatment. The knowledge and new strategies can not only help relatives to recognize depressive symptoms in, but also help them provide better support to, the depressed person and potentially prevent a depressive relapse and help to maintain recovery.

The intervention represents a holistic approach to treating depression by recognizing that depression not only affects the individual suffering from depression but also their wider social network. This relationship is two-way where poor family functioning could increase the risk of relapse whilst good family functioning could be a protective factor against depressive relapse. If this intervention reduces the risk of depressive relapse and promotes recovery it could also have a broader impact of decreasing the burden of disease. Systematic evaluation of the effect of FPE fills an important gap in current research by proposing the patient-relative relationship as a potential mechanism to influence outcome in depression.

The trial includes a heterogeneous group of patients with depression recruited from diverse geographically situated outpatient clinics as well as from private psychiatrists. Hence, it is hoped that results from this study will be highly generalizable to clinical practice. Implementation into daily practice can be further facilitated by the fact that the intervention is not expensive or complex.

